### Data/sample collection

#### Clinical data

Clinical evaluation and management is performed according to standard institutional procedures (Fig. 2). Collected clinical data, includes demographics, medical history, clinical symptoms, physical examination, disease course, laboratory measurements, as well as more advanced diagnostic information including microbiological (including an additional multiplex PCR), and serological investigations. A follow-up phone call 28-day after recruitment, defines the end of follow-up and generates data to be used by the expert panel (e.g. maximum disease severity, total use of antibiotics, Additional file 1).

#### Sample collection

For study purposes two blood samples, two nasal swabs and (in case of diarrhoea) a stool sample are collected (Fig. 2). Blood and nasal swabs sampling at two sampling points (at inclusion and after 3–5 days) is performed in hospitalized Dutch children in order to monitor the temporal dynamics of the host-pathogen interactions. One nasal swab sample (Universal Transport Medium, Copan, USA) is used for PCR based microbiological investigations performed for the establishment of patient diagnosis (only at inclusion). The PCR results are included in the eCRF and are available to the TAILORED-Treatment expert panel while determining the diagnosis of the patient (Fig. 2). The second nasal swab is collected in Transport Medium suitable for bacterial culturing (e-swab, Liquid Amies Medium, Copan), this sample is used for respiratory microbiome investigations and to develop a rapid detection technique for identification of microbial pathogens and antimicrobial resistances, based on mass spectrometry and proteomics for discovery of peptide biomarkers. Serum samples are used for different proteomic measurements, leukocytes are isolated for discovery of RNA-based biomarkers. Following RNA isolation, remaining DNA is used for GWAS studies. GWAS analyses is performed in the Netherlands, as Institutional review board (IRB) approval for genetic testing is not obtained in Israel. DNA collection is mentioned explicitly in the patient information. Blood samples are collected from children with a non-infectious disease only if blood sampling is required as part of their routine care. In cases of diarrhoea on enrolment, stool samples are collected. These samples will be evaluated to identify *Clostridium difficile* infections.

#### ‘Proteotyping’

Shotgun proteomic detection and identification of microorganisms, or ‘proteotyping’, relies on recognition of species-unique peptides by tandem mass spectrometry (MS), allowing discrimination of species facilitated at amino acid level resolution. The recent evolution of mass spectrometers, having high sensitivity, accuracy and resolution, enables detection of almost the complete proteome of a microorganism. With such analytical means, it is feasible to determine directly, within a clinical sample, the species identity, the sub-species strain type and the factors expressing virulence and antimicrobial resistance [35]. Clinical samples are processed by first removing human biomass and subsequently collecting bacteria. The proteins of the collected bacteria were processed by the LPI™ FlowCell or in-solution digestion protocols followed by liquid chromatography tandem MS (LC-MS/MS) analysis. The recently developed technology called Lipid-based Protein Immobilization (LPI™) is based on immobilization of biological material within a flow cell, followed by digestion of exposed proteins by an enzyme, such as trypsin [36–38]. The MS-based proteomics methodology has been applied successfully, without prior cultivations to the analyses of clinical nasal swab samples from the Sahlgrenska University Hospital that have been confirmed positive for a respiratory infectious bacterial species, i.e., *S. pneumoniae, H. influenza, M. catarrhalis and S. aureus* (unpublished data).

#### Central database

All clinical data (eCRFs) and research data (host biomarkers, host microbiome, pathogen identity and resistance) is coded and uploaded to a central, secured database (HoPOIT database) to which access is granted only to research partners (Fig. 3). The centralized clinical, microbiological, molecular and biochemical data is used to develop a multi-parametric model and diagnostic tools for differentiating between bacterial and viral infections.

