### Aetiology determination

Currently, no single reference standard exists for differentiating between bacterial and viral aetiology in an acute infectious disease. Therefore, we follow the Standards for Reporting of Diagnostic Accuracy (STARD) recommendation [39], and create a highly rigorous reference standard based on expert panel adjudication (Fig. 2). The eCRF of each patient is available to a panel of three independent physicians that are affiliated to the country of recruitment. Based on the information included in the eCRF, each member of the panel assigns one of the following diagnostic labels to each one of the patients: (i) bacterial infection; (ii) viral infection; (iii) mixed infection (i.e., bacterial and viral co-infection); (iv) non-infectious disease; or (v) undetermined. Of note, each expert is blinded to the research results and to the labels of his peers on the expert panel. For this purpose, mixed infection (bacterial and viral co-infection) is considered as bacterial infections, as they often elicit similar patient management. A final diagnosis is determined based on consensus agreement between all three experts (Fig. 2). The final diagnosis is used for the purpose of calculating the accuracy of the newly developed diagnostic tools. Cases with only majority agreement (2 out of 3 experts) are analysed as a separate sub-group. The remaining cases are labelled as undetermined. Specifically, this label is assigned in cases where each of the experts assigns a different diagnosis or in cases where 2 or more of the experts assign an “undetermined” diagnosis. These patients are used for data analysis and are expected to comprise roughly 10% of all patients.

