### Methods for computing the accuracy of a multi-parametric model

The multi-parametric model integrates various host-related and pathogen-related parameters into a single score that determines the likelihood of bacterial and viral aetiology (Fig. 3). The score is computed using a multinomial logistic regression formula that is developed during Stage A of the study. Using predetermined cut-offs, each of the patients is classified as bacterial, viral, or inconclusive (i.e., a marginal immune response that is neither clearly bacterial nor viral). The model diagnosis will be compared with the consensus diagnosis in order to determine its accuracy. The diagnostic accuracy is quantified by computing the following measures: sensitivity, specificity, positive predictive value, negative predictive value, total accuracy, positive likelihood ratio, negative likelihood ratio and diagnostic odds ratio. The area under the receiver operation curve is computed to perform cut-off independent comparisons of different diagnostic methods.

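### The model and the reference diagnosis draw on the same eCRF data, so any predictor the panel also sees leaves the primary accuracy liable to incorporation bias

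*Protocol article*

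**What the plan says.** All of this is in the protocol article.

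- **What the panel uses.** Aetiology determination: "Based on the information included in the eCRF, each member of the panel assigns one of the following diagnostic labels". Clinical data lists what is collected, including "laboratory measurements, as well as more advanced diagnostic information including microbiological (including an additional multiplex PCR), and serological investigations". Sample collection is explicit about the nasal swab: "The PCR results are included in the eCRF and are available to the TAILORED-Treatment expert panel while determining the diagnosis of the patient".
- **What the panel does not see.** Aetiology determination: "each expert is blinded to the research results and to the labels of his peers on the expert panel".
- **What goes into the database.** The section Central database describes the content: "All clinical data (eCRFs) and research data (host biomarkers, host microbiome, pathogen identity and resistance) is coded and uploaded to a central, secured database". The same section then says: "The centralized clinical, microbiological, molecular and biochemical data is used to develop a multi-parametric model and diagnostic tools".
- **What the model contains.** The section on computing accuracy describes it thus: "The multi-parametric model integrates various host-related and pathogen-related parameters into a single score". No predictors are named there.
- **How it is judged.** The model's classification is compared with the panel consensus, and its sensitivity and specificity are the primary endpoint. Study stages describes Stage B as an independent cohort of about 300 patients and gives no different reference standard for it.

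**The concern.** An item that helps to form the reference label and is also a predictor makes index test and reference agree partly by construction. Where the item is wrong and the panel follows it, the shared error is counted as a correct classification. This is incorporation bias.

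The article itself gives a reason to expect such errors. Limitations of current diagnostic tools reports that *S. pneumoniae* is carried by up to 68% of healthy children, and that respiratory viruses were found in 35.4% of asymptomatic children. Detecting an organism therefore does not settle the aetiology.

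At stake is the primary endpoint. An independent validation cohort protects against overfitting. It does not protect against this, because the dependence is built into the label and recurs in Stage B. The planned AUC comparisons between diagnostic methods are exposed too: a method that uses panel-seen items would be favoured over one that uses only blinded biomarkers.

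**Working it through.** The plan gives no figure to reproduce. The check traces the data flow and then illustrates direction and size under stated assumptions.

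**1. Data flow**

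| Data | Seen by panel? | In the data used to develop the model? |
|---|---|---|
| eCRF clinical and laboratory items | Yes (Clinical data; Aetiology determination) | Yes (Central database) |
| Nasal PCR result | Yes (Sample collection) | Yes, as eCRF and microbiological data (Clinical data with Central database) |
| Host biomarkers, microbiome, research pathogen identity and resistance | No (Aetiology determination) | Yes (Central database) |

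Central database itself separates eCRF data from research data, so the blinding covers only the last row. The overlap is in the data used for development. The article does not say which items remain as final predictors.

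**2. One shared item used as the whole test**

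From the protocol: null value 70%, and a 1:3 bacterial-to-viral ratio in children, so prevalence 25%. Assumed: the item has sensitivity and specificity 70%; the panel follows it in 20% of cases and is right in the other 80%. T is the item, R the panel label.

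- P(T+) = 0.25 × 0.70 + 0.75 × 0.30 = 0.40
- P(R+) = 0.80 × 0.25 + 0.20 × 0.40 = 0.28
- P(T+ and R+) = 0.80 × 0.175 + 0.20 × 0.40 = 0.22
- Apparent sensitivity = 0.22 / 0.28 = 78.6%
- P(R−) = 1 − 0.28 = 0.72
- P(T− and R−) = 0.80 × 0.525 + 0.20 × 0.60 = 0.54
- Apparent specificity = 0.54 / 0.72 = 75.0%

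**3. Shared item as one predictor among others**

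A simulation with all inputs assumed: 25% bacterial; one panel-blinded biomarker (shift 1.5 SD); other panel information (shift 2 SD); and one shared item that is 70% or 80% accurate. The panel calls a case bacterial when its log-odds exceed zero. It gives the shared item a weight of 0 to 3 times its log-likelihood ratio, where 1 is the correct weight. A logistic model was fitted on one half and tested on the other.

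| Item accuracy | Panel weight | AUC v panel: item out / in | AUC v truth: item out / in | Item in: panel minus truth |
|---|---|---|---|---|
| 70% | 0 | 0.742 / 0.764 | 0.854 / 0.888 | −0.124 |
| 70% | 1 | 0.756 / 0.838 | 0.855 / 0.871 | −0.033 |
| 70% | 2 | 0.737 / 0.890 | 0.854 / 0.853 | +0.037 |
| 70% | 3 | 0.704 / 0.924 | 0.854 / 0.849 | +0.075 |
| 80% | 0 | 0.743 / 0.790 | 0.856 / 0.925 | −0.135 |
| 80% | 1 | 0.775 / 0.909 | 0.857 / 0.915 | −0.006 |
| 80% | 2 | 0.744 / 0.958 | 0.857 / 0.914 | +0.044 |
| 80% | 3 | 0.709 / 0.980 | 0.856 / 0.913 | +0.067 |

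At weights 1 to 3, adding the item raises AUC against the panel by 0.082 to 0.271. Against the truth the change is −0.005 to +0.058. The measured AUC exceeds the true AUC only at weights 2 and 3.

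On the primary-endpoint scale, with the cut-off set so that the model calls the same proportion bacterial as the panel:

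- Weights 2 and 3: sensitivity is overstated by 4.5 points (0.668 v 0.623) to 10.8 points (0.889 v 0.781), and specificity by 0.9 points (0.893 v 0.884) to 10.0 points (0.951 v 0.851).
- Weight 1: sensitivity differs by −2.1 and +0.7 points, and specificity by −2.4 and −1.3 points, for the 70% and 80% items.

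The simulation uses one panel label. It does not model the unanimity rule or the inconclusive class.

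**The case against.** The strongest reply is that the overlap in final predictors is inferred. Primary objective and the accuracy-methods section describe host- and pathogen-related factors. These match the research data to which the panel is blinded. Sample collection assigns the PCR swab to establishing the diagnosis and a second swab to research. Data can be used in development as labels or descriptors without becoming predictors. The figure on model development is not shown, and a predictor list may sit in the analysis plan.

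Much of this stands, and it limits the point in three ways.

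- A reader might infer that the nasal PCR is a model predictor. No section says so. It follows only as a possibility, from counting PCR as clinical data and using the centralized clinical and microbiological data for development.
- A reader might infer that the reported accuracy is inflated as a matter of fact. The documents do not show that, and the simulation finds no excess in AUC when the panel weights the shared item correctly.
- A reader might infer that the contribution of the novel biomarkers can no longer be isolated. Secondary objectives and Secondary endpoints contradict this. They plan sensitivity and specificity for individual host blood markers, and for sets of them, from research results the panel does not see. These are not affected in this way unless a marker is also a routine eCRF value.

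The 79%/75% illustration also treats one item as the whole test and the panel as otherwise perfect. The actual panel has three mutually blinded experts, 28-day follow-up data and a unanimity rule.

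The reply does not remove the core. The point does not complain of a missing predictor list. Central database affirmatively names clinical and microbiological data as the basis for the model, without limiting them to blinded items, and the stated blinding does not reach the eCRF.

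**Conclusion.** The concern holds in conditional form. The stated data flow lets items used for the reference diagnosis enter the model. If any does, the primary-endpoint sensitivity and specificity are liable to be inflated, and Stage B will not reveal or correct it.

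The size cannot be fixed from the document. Under the assumptions above it ranges from no excess in AUC (shared item weighted correctly, where other reference error pulls the estimate down) to about 0.04 to 0.08 in AUC when the panel over-weights the item. The 9-point and 5-point gains in sensitivity and specificity (79% and 75% against 70%) apply only to a single shared item standing alone.

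**What to change.** In Central database and in Methods for computing the accuracy of a multi-parametric model, state that items the panel sees (eCRF clinical, laboratory and PCR results) serve the reference standard and are not predictors in the primary-endpoint model.

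If any such item is kept, pre-specify two things:

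- Stage B sensitivity and specificity are also reported for the model refitted on panel-blinded measurements only (host RNA and protein, microbiome, proteotyping).
- Any claim of accuracy independent of the panel's inputs rests on that version.

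The cost is wording and at most one extra model fit on data already collected. The downside is a possibly lower headline accuracy. In the simulation at weights 1 to 3, the model without the shared item scored 0.70 to 0.78 in AUC against the panel and about 0.86 against the truth, so the restricted figure may err on the low side.

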**Fig. 3 Fig3:**
[figure not shown]
Development of the multi-parametric model

### Aetiology determination

Currently, no single reference standard exists for differentiating between bacterial and viral aetiology in an acute infectious disease. Therefore, we follow the Standards for Reporting of Diagnostic Accuracy (STARD) recommendation [39], and create a highly rigorous reference standard based on expert panel adjudication (Fig. 2). The eCRF of each patient is available to a panel of three independent physicians that are affiliated to the country of recruitment. Based on the information included in the eCRF, each member of the panel assigns one of the following diagnostic labels to each one of the patients: (i) bacterial infection; (ii) viral infection; (iii) mixed infection (i.e., bacterial and viral co-infection); (iv) non-infectious disease; or (v) undetermined. Of note, each expert is blinded to the research results and to the labels of his peers on the expert panel. For this purpose, mixed infection (bacterial and viral co-infection) is considered as bacterial infections, as they often elicit similar patient management. A final diagnosis is determined based on consensus agreement between all three experts (Fig. 2). The final diagnosis is used for the purpose of calculating the accuracy of the newly developed diagnostic tools. Cases with only majority agreement (2 out of 3 experts) are analysed as a separate sub-group. The remaining cases are labelled as undetermined. Specifically, this label is assigned in cases where each of the experts assigns a different diagnosis or in cases where 2 or more of the experts assign an “undetermined” diagnosis. These patients are used for data analysis and are expected to comprise roughly 10% of all patients.

### Study stages

The study is conducted in two consecutive stages. Stage A is used to collect molecular, biochemical, microbiological and clinical data on a group of approximately 900 patients. Collected data is used to develop unique diagnostic signatures able to distinguish between bacterial and viral aetiologies, a mass spectrometry based rapid detection technique for identification of microbial pathogens and antimicrobial resistances and a personalized treatment algorithm for tailored antimicrobial therapy that integrates clinical, molecular and biochemical data. In stage B, a second, independent cohort of approximately 300 patients is recruited for the purpose of testing and validating the performances of the multi-parametric model.

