## Methods

### General study design

In this prospective, multi-centre, observational study, an expected total number of 1200 paediatric and adult patients aged 1 month and older with suspected LRTI and/or sepsis or a non-infectious disease are recruited, in order to develop a diagnostic model to differentiate between bacterial and viral infections. The study will generate a model for patients with LRTI and a separate model for patients with sepsis. The prediction of the model obtained from each patient will be compared with a consensus diagnosis by a panel of three experts in order to determine its accuracy (Fig. 2). The study is a non-interventional study, and therefore, the diagnostic prediction of the model will not be used for any clinical or diagnostics decision making. Local data monitor plans were used and executed by local, independent monitors.

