#### Paediatric population analysis

First, we estimate the sample size required to reject the null hypothesis that the sensitivity over the entire population, P, is lower than P0 = 70% (H0: P ≤ P0, H1: P > P0) with significance level of 1% (α = 0.01), power of 80% (=1-β) for a true sensitivity P1 of 90% (P1 - P0 ≥ 0.2). For sufficiently large sample sizes (n > ~ 30) the sample distribution of the sensitivity, is approximately normally distributed, ($$ \widehat{p} $$ ~ N{P, P(1-P)/n}). Thus, the number of bacterial patients that are required is:$$ \mathrm{n}=\frac{{\left({\mathrm{Z}}_{1-\upalpha}\sqrt{{\mathrm{P}}_0\left(1-{\mathrm{P}}_0\right)}+{\mathrm{Z}}_{1-\upbeta}\sqrt{{\mathrm{P}}_1\left(1-{\mathrm{P}}_1\right)}\right)}^2}{{\left({\mathrm{P}}_1-{\mathrm{P}}_0\right)}^2}\le 76 $$

We estimate that the ratio between bacterial and viral paediatric patients is 1:3 and that expert consensus is achieved in 65% of the cases. Thus, the number of patients with an acute infection required in order to reach 76 bacterial patients is 468 = (76 / 25% / 65%). Using similar considerations for computing specificity the sample size for viral patients is also 76. Of note, we anticipate that the above mentioned 468 patients will include 229 (= 468 × 75% × 65%) viral patients, and thus there is no need for additional patients. To assess the host-response based diagnostics accuracy in differentiating patients with an acute infection (both viral and bacterial) and non-infectious patients, assuming P0 = 70% (H0: P ≤ P0, H1: P > P0) with significance level of 1% (α = 0.01), power of 80% (=1-β) for a true sensitivity P1 of 90% (P1 - P0 ≥ 0.2) requires 76 non-infectious patients. Overall, the paediatric cohort should include at least 468 patients with a suspected infectious disease and 76 patients with non-infectious.

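### The accuracy tests are sized on almost the whole study, but the model is tested only in Stage B (about 300 patients), which cannot deliver the stated power for paediatric sensitivity or adult specificity

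*Protocol article*

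**What the plan says.** The primary endpoint is the model's sensitivity and specificity for bacterial against viral aetiology in patients with LRTI and/or sepsis. No age group is named there.

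The sample size sections work by age group. Each test has H0: P ≤ 70%, a significance level of 1%, and 80% power if the true value is 90%. Each age group is said to need 76 bacterial and 76 viral patients with a consensus diagnosis. For children the plan assumes that "the ratio between bacterial and viral paediatric patients is 1:3 and that expert consensus is achieved in 65% of the cases", and it concludes: "Overall, the paediatric cohort should include at least 468 patients with a suspected infectious disease and 76 patients with non-infectious". For adults, a viral to bacterial rate of 3:7 and the same consensus rate give 390 infectious patients, plus 76 non-infectious. Neither section mentions a stage.

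Study stages gives Stage A about 900 patients, whose data are used to develop the diagnostic signatures. Of Stage B it says: "a second, independent cohort of approximately 300 patients is recruited for the purpose of testing and validating the performances of the multi-parametric model". The section on computing accuracy agrees about where the model comes from: "The score is computed using a multinomial logistic regression formula that is developed during Stage A of the study". It adds that patients are classified by cut-offs set in advance.

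General study design describes the comparison more loosely: "The prediction of the model obtained from each patient will be compared with a consensus diagnosis by a panel of three experts".

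**The concern.** The calculation counts 468 + 390 = 858 infectious patients towards the tests. With 2 × 76 non-infectious patients it reaches 1010 of the 1200 expected. Only about 300 patients are in the cohort recruited to test the model, so the two parts of the plan do not describe the same analysis.

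If accuracy is assessed in Stage B, the counts behind the stated power are not available there. If Stage A patients are counted to reach them, accuracy is measured on the data used to build the model. With biomarkers selected from multi-omics data, that biases the estimate upward and undermines the test against 70%.

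The two measures affected are sensitivity in children and specificity in adults. These tell a reader how often bacterial disease in a child would be missed, and how often viral disease in an adult would be called bacterial.

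**Working it through.** **Inputs from the protocol.** P0 = 0.70, P1 = 0.90, one-sided α = 0.01, target power 80%. Consensus rate 65%. Children 25% bacterial and 75% viral; adults 70% bacterial and 30% viral. Infectious patients 468 and 390. Stage B about 300.

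**The plan's own figures.**
- 76 / 0.25 / 0.65 = 467.7, so 468 children. 76 / 0.30 / 0.65 = 389.7, so 390 adults. Both follow from 76.
- The 76 itself does not follow from the printed formula: (2.326 × √0.21 + 0.842 × √0.09)² / 0.2² = 43.5, so 44. The plan prints 76 as an upper bound. This is a separate point; the shortfall below is checked against both values.

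**Stage B counts (assumption: Stage B mirrors the planned mix).** Consensus fractions of infectious patients are 0.25 × 0.65 = 0.1625 (bacterial children), 0.75 × 0.65 = 0.4875 (viral children), 0.70 × 0.65 = 0.455 (bacterial adults) and 0.30 × 0.65 = 0.195 (viral adults). Three ways of scaling to 300 give the range:

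| Scaling | Infectious children / adults | Bacterial children | Viral children | Bacterial adults | Viral adults |
|---|---|---|---|---|---|
| 300/1200 (the 190 patients beyond 1010 add none) | 117 / 97.5 | 19.0 | 57.0 | 44.4 | 19.0 |
| 300/1010 (planned mix) | 139.0 / 115.8 | 22.6 | 67.8 | 52.7 | 22.6 |
| 300/858 (no non-infectious patients in Stage B) | 163.6 / 136.4 | 26.6 | 79.8 | 62.0 | 26.6 |

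**Power in the two scarce groups.** Exact binomial: take the smallest r with P(X ≥ r | 0.70) ≤ 0.01; power is P(X ≥ r | 0.90).
- n = 19: all 19 must be correct; power 0.9^19 = 13.5%.
- n = 23: 22 must be correct; power 23 × 0.9^22 × 0.1 + 0.9^23 = 0.226 + 0.089 = 31.5%.
- n = 24: 29%. n = 25: 54%. n = 26: 51%. n = 27: 48%. The sequence is saw-toothed because r is an integer.
- The plan's normal approximation at n = 23: Φ((0.2 × √23 − 2.326 × √0.21) / 0.3) = Φ(−0.356) = 36%. The plan itself reserves that approximation for n above about 30.

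**The other groups at the 300/1010 mix.** Bacterial adults, n = 53: 92%. Viral children, n = 68: 96%.

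**Pooled over age at the 300/1010 mix.** Bacterial 22.6 + 52.7 = 75.3, power 98%. Viral 67.8 + 22.6 = 90.4, power 99%. At the leanest scaling (63 and 76 patients) the same calculation gives 95% and 98%.

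**Could another allocation of the 300 rescue both scarce groups?** At the planning rates, 44 in each needs 44/0.1625 + 44/0.195 = 271 + 226 = about 496 infectious patients. 76 in each needs about 857. Neither fits in 300, so raising one group lowers the other.

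**The case against.** The strongest reply is that the protocol never says the tests are run by age group within Stage B. The primary endpoint names no age stratum, and the sample size section describes its purpose as developing a model. Read that way, Stage B pooled over age is amply powered. This stands as far as it goes, and it means that Stage B as a whole is not too small. It does not remove the conflict, because the only power calculation given is age-specific and its counts cannot be met in Stage B.

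A second reply is that the Stage B mix is not stated, so no single power figure can be attached to it. That is correct. A reader might take 32% as the power of the plan; it is one point on a saw-toothed curve under one assumed split. What holds over the proportional splits examined is that power stays well below 80% in both scarce groups.

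A reader might also infer from the general design sentence about each patient that the primary accuracy will be computed largely on development data. The text does not support that. The sentence describes the comparison with the panel and does not define an analysis set, while the plan provides an independent cohort and cut-offs set in advance. The upward bias would arise only if Stage A patients were counted to make up the numbers.

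Nor do the documents support a joint success probability, since nothing requires all the tests to succeed together. A further division of Stage B between the LRTI and sepsis models would shrink the groups, but no split is given from which to calculate it.

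**Conclusion.** The concern holds in a conditional form. The stated 80% power per age group cannot be delivered by Stage B for paediatric sensitivity or adult specificity. Under proportional splits each of those groups has about 19 to 27 patients and about 14% to 54% exact power. The shortfall remains whether the requirement is 76 or 44.

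This rests on the plan's own aetiology ratios and 65% consensus rate, on reading Stage B as the only stage that tests the model, and on an assumed Stage B mix. It does not extend to bacterial adults or viral children at the planned mix, nor to an age-pooled Stage B analysis. The protocol is wrong as written because its sample size section and its stage sizes describe different analysis sets; an independent validation is already planned.

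**What to change.** State in the sample size and accuracy sections that the primary sensitivity and specificity, and the tests against 70%, use Stage B patients only, with the formula and cut-offs fixed after Stage A. Then choose one of two courses:

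1. Make the age-pooled Stage B estimate the powered primary analysis, and report results by age group as estimates with exact confidence intervals.
2. Keep the age-specific tests and restate their power for the numbers Stage B can supply: a range, conditional on the assumed mix, that is well below 80% for paediatric sensitivity and adult specificity.

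Either way, give the expected Stage B composition by age group and aetiology so that the power statement can be checked. The cost is wording and, under the second course, a less favourable stated power. No extra patients and no new division between the stages are needed.
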